#### 2.2.4. Recruitment

Participants will be recruited from the outpatient department of Daejeon University Daejeon Korean Medicine Hospital by posting brochures on the bulletin board and Internet homepage of the clinical trial center. For additional promotions, newspaper leaflets and local advertisements on subways, buses, and apartment notice boards will be considered, if needed.

### 2.3. Randomization and Allocation Concealment

Randomization will be conducted by an independent statistician by using a computer random number generator in SAS^®^ version 9.4 (SAS institute. Inc., Cary, NC, USA). Based on a generated random-number table, the participants will be allocated to the standard-dose USL, high-dose USL, and control groups in a 1:1:1 ratio. The manufacturer, who is responsible for the management of the random allocation sequence, will label the clinical trial medications according to the randomization list and deliver them to the management pharmacist on the trial site. When the investigator requests the trial medication, the management pharmacist will provide the corresponding medication using the participant’s randomization code.

### 2.4. Blinding

All participants and investigators, including outcome assessors, will be blinded throughout the trial. The trial medication was packaged identically with a placebo developed to have the same color, taste, and smell as the USL intervention medicine. The subject identification code will be sealed in an opaque envelope, stored in a locked cabinet, and not disclosed until the end of the trial, except if a serious adverse reaction occurs.

### 2.5. Intervention

The trial medication, USL, and placebo were produced by the National Institute of Korean Medicine Development. USL is an extract of AR, and one tablet (800 mg) of USL contains 500 mg of AR extract. The placebo does not contain the major ingredient of USL but contains starch, lactose, and colorants. Both drugs were manufactured as round and brown tablets. The dosage was determined based on the results of a previous experimental study that reported a lack of toxicity and genotoxicity of USL and the experimental study results, and USL was found to have no toxicity and genotoxicity in a previous study [29]. The standard-dose USL group will be administered one tablet of USL and one tablet of the placebo twice daily for 12 weeks; the high-dose USL group will be administered two tablets of USL twice daily for 12 weeks; and the control group will be administered two tablets of the placebo twice daily for 12 weeks.

Participants will be provided with the trial medication at week 0 and week 6 and asked to return to calculate medication compliance. The overall compliance should be at least 75%, and those with <75% will be excluded from the per-protocol (PP) analysis.

### 2.6. Outcomes

#### 2.6.1. Primary Outcome

The primary outcomes of this trial include both objective and subjective outcome measures recommended by the Ministry of Food and Drug Safety of Korea. For objective outcomes, TBUT was chosen as the primary outcome to assess tear film stability, and for subjective outcomes, OSDI will be assessed to evaluate symptoms and discomfort related to DED.

##### Tear Break-Up Time (TBUT)

TBUT was chosen as the primary outcome for objective signs in our study because TBUT assesses tear film stability, which is one of the essential diagnostic criteria for diagnosing tear film abnormalities and DED [37]. TBUT is also one of the most frequently used diagnostic tests in clinical practice for DED [38].

The procedure follows a standardized methodology. For the TBUT test, subjects will be instructed to sit at the slit-lamp microscope with their chin on the chin rest. Sodium fluorescein will then be applied to both eyes on the inferior temporal bulbar conjunctiva. Each participant will be instructed to blink naturally three times to distribute fluorescein on the ocular surface. Then, the participants will be asked to cease blinking until instructed otherwise. The time between eye opening and the first appearance of a dry spot in the tear film will be measured in seconds using a slit-lamp microscope (BQ-900; Haag-Streit, Bern, Switzerland). The cut-off value of TBUT for the diagnosis of DED is reported to be less than 10 s for an abnormal tear film, between 5 s and 10 s for a marginal tear film, and less than 5 s for severe DED [39]. With reference to this, participants with a TBUT ≤ 10 s will be included in this trial. The TBUT for each participant will be measured at screening, week 6, week 12, and week 14, and we will measure the changes in mean TBUT from screening to week 12 between the intervention and control groups as the primary outcome.

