## 2. Method and Analysis

### 2.1. Trial Design

This study is a phase 2, dose-finding, double-blind, randomized placebo-controlled trial to evaluate the efficacy and safety of two different doses of USL, compared with a placebo, for DED treatment. The trial will be conducted at Daejeon University Daejeon Korean Medicine Hospital and is set to start recruitment in January 2025. Participants who sign a written informed consent form after receiving a comprehensive explanation of the trial will be screened, and 120 participants will be enrolled after the eligibility assessment. Eligible subjects will be randomized into three groups in a 1:1:1 allocation ratio: standard-dose USL (1 g/day), high-dose USL (2 g/day), and placebo groups. The subjects would be asked to administer one of the medications twice a day for 12 weeks and visit five times (at screening, baseline, week 6, week 12, and week 14) to evaluate the efficacy and safety outcomes (Figure 1, Table 1). This study follows the guidelines of the Standard Protocol Items: Recommendations for Interventional Trials (SPIRIT) [30] and will be conducted in compliance with ethical principles in the Declaration of Helsinki and Good Clinical Practice guidelines [31].

This study protocol was approved by the Institutional Review Board of Daejeon University Daejeon Korean Medicine Hospital (DJDSKH-23-DR-11), and registered at Clinicaltrials.gov (NCT06016010).

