### 2.2. Participants

#### 2.2.1. Inclusion Criteria

Participants who meet the following criteria will be enrolled in this trial: (1) subjects aged over 19 years; (2) subjects with dry eye symptoms (stiffness, foreign body sensation, irritation, bloodshot eyes, itching, blurred vision, pain, etc.) for at least 3 months; (3) subjects who have had both eyes screened, with a corrected visual acuity of 0.2 or more; (4) subjects with a fluorescein corneal staining score (Oxford grading) ≥ 2, tear break-up time (TBUT) ≤ 10, and Schirmer’s test ≤ 10 mm at screening; (5) subjects with an Ocular Surface Disease Index (OSDI) ≥ 23 at screening; and (6) subjects who voluntarily agree and provide written informed consent to participate in the clinical trial.

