
#### 2.2.3. Sample Size

The estimated sample size required for this trial is 120 patients (40 patients per group), based on previous comparable studies [34,35,36]. Although we could not calculate the sample size based on the exact effect size, as our study is the first trial using USL on patients with DED, we calculated the sample size based on previous studies expected to have similar effects. We assumed the difference in the changes in TBUT as 1.3, and the standard deviation (SD) as 1.8 from baseline to post-intervention between the control and standard-dose USL groups. The power to detect differences is assumed to be 0.8, with the two-sided significance level set at 0.05. The ratio of the allocation of subjects between groups is 1:1:1, and the dropout rate is assumed to be 0.2.

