##### Ocular Surface Disease Index (OSDI)

The OSDI is the primary outcome measure of subjective symptoms in this trial. It is the most commonly used questionnaire for patients with DED in clinical trials. The OSDI has been validated to measure the severity of DED, and it comprises psychometric symptoms related to DED [40]. Owing to its strong establishment in DED, a consensus to use the OSDI was reached by a related committee [15].

The OSDI measures the frequency of symptoms, environmental triggers, and vision-related quality of life within 1 week. It comprises 12 questions, each of which is graded on a scale of 0–4, where 0 indicates none of the time, 1 as some of the time, 2 as half of the time, 3 as most of the time, and 4 as all of the time [40]. The total OSDI score is calculated as follows: OSDI = [(sum of scores for all questions answered) × 100]/[(total number of questions answered) × 4]

Thus, the OSDI score ranges from 0 to 100; the higher the score, the worse the quality of life. According to OSDI scores, patients can be categorized as having normal (0 to 12 points), mild (13 to 22 points), moderate (23 to 32 points), or severe (33 to 100 points) ocular surface disease. In our trial, patients with OSDI scores ≥ 23 points will be included, meaning that those who have moderate-to-severe symptoms will all be included. The OSDI score will be measured at screening, week 6, week 12, and week 14, and the changes in OSDI from screening to week 12 will be the primary outcome of this trial.

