### 2.7. Statistical Analysis

Statistical analyses of all outcomes will be conducted by an independent statistician using SAS Version 9.4 Analytics Pro software. Continuous variables will be presented as the mean ± SD and categorical variables will be presented as frequencies and percentages. For efficacy analysis, a full analysis set (FAS) based on intention-to-treat (ITT) analysis will be performed as the primary analysis, and PP analysis will be used for secondary analysis. All randomized participants who are evaluated at least once after administration of the trial medication will be included in the FAS, and only those who complete the trial without violating the protocol will be included in the PP set. A safety analysis will be conducted for all participants who are randomized and administered the trial medication at least once.

The primary and secondary efficacy outcomes will be analyzed using the mixed-effects model for repeated measures, with each group and visit set as fixed effects and participants as random effects. In addition, the difference between pre- and post-treatment within groups will be analyzed using Student’s paired *t*-test or Wilcoxon signed-range test, depending on normality. A multiple imputation method will be used for missing values. The efficacy of USL will be accepted at a significance level of 2.5% in both TBUT and OSDI compared with the placebo, whereas other secondary outcomes will be accepted at a 5% significance level.

To analyze safety outcomes, Fisher’s exact test will be used to compare the number of AEs between the groups, and Student’s paired *t*-test or the Wilcoxon signed-rank test will be performed to analyze the differences between pre- and post-treatment laboratory variables, vital signs, visual acuity, and IOP. Demographic characteristics will be analyzed using the Wilcoxon rank-sum test or independent *t*-test for continuous variables and Fisher’s exact test or the chi-square test for categorical variables.

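### TBUT, OSDI and corneal staining have no week-0 reading, so the planned within-group pre-post tests start from the selected screening value and lean toward improvement in every arm; the comparison with placebo is not biased

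*Protocol article*

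**What the plan says.** **Measurement times.** Under the TBUT heading: "The TBUT for each participant will be measured at screening, week 6, week 12, and week 14". Under the OSDI heading: "The OSDI score will be measured at screening, week 6, week 12, and week 14". The staining section gives the same four time points. Table 1 agrees: TBUT, OSDI and staining are marked at Visit 1 (-2 weeks) and blank at Visit 2 (week 0). VAS, Schirmer's test, the meibomian gland test, SPEED-II and the biomarkers are marked at week 0.

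**Selection.** Section 2.2.1 makes the screening readings entry criteria: "tear break-up time (TBUT) ≤ 10", OSDI of at least 23, and Oxford staining grade of at least 2.

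**Primary change.** For TBUT, "we will measure the changes in mean TBUT from screening to week 12 between the intervention and control groups as the primary outcome". For OSDI, "the changes in OSDI from screening to week 12 will be the primary outcome of this trial".

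**Analysis.** Section 2.7 compares groups with a mixed model for repeated measures and accepts efficacy at 2.5% on both TBUT and OSDI against placebo. In the same efficacy paragraph it adds that "the difference between pre- and post-treatment within groups will be analyzed using" a paired t-test or a Wilcoxon signed-rank test.

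**Baseline.** Section 2.1 has participants "visit five times (at screening, baseline, week 6, week 12, and week 14". Section 2.2.3 words the planning difference as "from baseline to post-intervention between the control and standard-dose USL groups".

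**The concern.** A participant enters only if the screening reading is bad enough. Part of any single reading is measurement error and day-to-day variation, so among those admitted the error component is, on average, on the bad side. At the next reading that component averages zero, and the mean moves toward better values without any treatment.

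For TBUT, OSDI and staining, the screening reading is the only one before treatment. The within-group paired test therefore takes as its starting point the value that admitted the participant, and its null hypothesis of no mean change is false even when the drug and placebo do nothing. A statement that the USL arms improved significantly from before treatment could then be partly or wholly an artefact. In a dose-finding trial such a statement can easily be read as evidence for each dose.

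**Working it through.** **1. The plan's own figure.** Inputs from section 2.2.3: difference 1.3, SD 1.8, two-sided 5%, power 0.8, dropout 0.2.

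n = 2 × (1.960 + 0.842)² × 1.8² / 1.3² = 2 × 7.849 × 3.24 / 1.69 = 30.1, so 31 per arm. The t-based version gives 32, and 32/0.8 = 40 per arm, 120 in total. The stated figure reproduces. I use 32 completers per arm below.

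**2. Expected change with no effect.** Assume each reading is a stable true value plus independent error, with unselected mean μ, SD σ and test-retest reliability ρ. With cut-off c and a = (c − μ)/σ, the expected shift from screening to a later reading is

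(1 − ρ) × σ × φ(a)/P,

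where P is the proportion admitted: Φ(a) for TBUT, 1 − Φ(a) for OSDI. The cut-offs are in section 2.2.1. The values of μ, σ and ρ are not in the article; they are assumptions, shown over a range.

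- TBUT, μ = 8, σ = 3, c = 10: a = 0.667, φ = 0.3194, P = 0.7475. 3 × 0.3194/0.7475 = 1.28. Times 0.5 = 0.64 s; times 0.3 = 0.38 s.
- OSDI, μ = 25, σ = 15, c = 23: a = −0.133, φ = 0.3954, P = 0.5530. 15 × 0.3954/0.5530 = 10.7. Times 0.5 = 5.4 points; times 0.3 = 3.2 points.

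**3. Rejection by the paired test.** I simulated the same model with no treatment, placebo or time effect, selected on screening only, and applied a two-sided 5% paired t-test with n = 32. The SD of change is the one the model itself produces after selection.

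| Endpoint (μ, σ) | ρ | Shift toward improvement | SD of change | Rejection |
|---|---|---|---|---|
| TBUT (6, 3) | 0.5 | 0.27 s | 2.90 | 8% |
| TBUT (6, 3) | 0.7 | 0.16 s | 2.28 | 7% |
| TBUT (7, 3) | 0.5 | 0.43 s | 2.86 | 13% |
| TBUT (7, 3) | 0.7 | 0.26 s | 2.26 | 10% |
| TBUT (8, 3) | 0.5 | 0.64 s | 2.82 | 24% |
| TBUT (8, 3) | 0.7 | 0.38 s | 2.24 | 15% |
| OSDI (25, 15) | 0.5 | 5.4 | 13.8 | 57% |
| OSDI (25, 15) | 0.7 | 3.2 | 11.1 | 36% |
| OSDI (30, 15) | 0.5 | 3.9 | 14.0 | 34% |
| OSDI (30, 15) | 0.7 | 2.4 | 11.2 | 21% |
| OSDI (35, 18) | 0.5 | 3.8 | 16.9 | 24% |
| OSDI (35, 18) | 0.7 | 2.3 | 13.5 | 15% |

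**4. Wider range.** If the population lies far from the cut-off, the problem almost vanishes: TBUT (5, 2) gives a shift of at most 0.02 s and 5% rejection; OSDI (50, 15) gives 0.1-0.6 points and 5-6%. If it lies on the cut-off, the problem is large: TBUT (10, 3) with ρ = 0.5 gives 1.20 s, close to the planned effect of 1.3 s.

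**5. With a week-0 reading that plays no part in selection.** In the same model the mean week-0 to week-12 change is about zero (TBUT within 0.005 s, OSDI within 0.03 points) and the paired test rejects 4.3-5.6% of the time.

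**6. Between arms.** Selection acts equally on all randomised arms. The simulated two-sample test on change kept its level: 2.4% (TBUT) and 2.3% (OSDI) at a nominal 2.5%.

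**7. Precision.** As baseline covariate in place of screening, a week-0 reading lowers residual variance by about 2-8%. With both readings as covariates the ratio to screening alone is [1 − 2ρ²/(1 + ρ)]/(1 − ρ²): 0.667/0.750 = 0.89 at ρ = 0.5 and 0.424/0.510 = 0.83 at ρ = 0.7, that is 11-17% lower.

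**The case against.** The strongest reply is that the protocol already decides efficacy against placebo. Section 2.7 ties acceptance to that comparison, the primary TBUT change is defined between groups, and the paired tests are supplementary and carry no decision rule. This stands. A reader might infer that the primary result or the efficacy decision is biased; the documents do not support that, since regression to the mean cancels between randomised arms.

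Second, the size is unknown. This also stands. A reader might infer that placebo will show significant improvement. Only the expected direction follows from the design; significance depends on a mean, SD and reliability that the article does not give.

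Third, a reader might infer that starting from screening costs the comparison much precision. It does not: exchanging screening for week 0 gains only about 2-8% in adjusted residual variance, and for unadjusted change the screening start has a slightly smaller SD (TBUT 2.82-2.89 against 3.00 at ρ = 0.5). The larger gain comes from having a second reading.

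Fourth, the word baseline in section 2.2.3 may be read as contradicting the endpoint definition. It is ordinary generic wording, and the outcome sections and Table 1 consistently fix screening as the start. Screening as baseline is a legitimate choice in a randomised placebo-controlled trial.

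What the reply does not remove is that the paired tests are stated in the efficacy paragraph, and for these three measures they test a null that selection makes false. A statistical analysis plan cannot supply a reading that the schedule does not collect.

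**Conclusion.** The point holds for the within-group tests only. For TBUT, OSDI and corneal staining these tests are biased toward improvement in every arm, because their only pre-treatment value is the one used for selection. The direction follows from the design.

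The size rests on the assumed population values and on a model of stable true values with independent normal errors: about 0.2-0.6 s and 7-24% rejection on placebo for TBUT, about 2-5 points and 15-57% for OSDI, with near-nominal rates if most participants lie well beyond the cut-offs. I did not quantify staining. The primary inference stands, so this is a correction to make rather than a fault in the trial's main comparison.

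**What to change.** **Section 2.7 (wording only).** Drop the within-group paired tests as efficacy evidence. Report within-arm changes descriptively, with a note that the screening values of TBUT, OSDI and staining were selected by the entry criteria. State that every efficacy conclusion, secondary as well as primary, rests on the contrast with placebo. This is needed even if a week-0 reading is added, because such a reading does not remove placebo response or natural course.

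**Schedule (optional).** Add TBUT and OSDI at Visit 2 before allocation, and keep screening for eligibility. Use the week-0 value alone for any within-arm change; averaging it with screening would put about half of the selection effect back. Use both readings as covariates in the between-arm model, which lowers residual variance by about 11-17% against screening alone under the same assumptions. The cost is a 12-item questionnaire and one fluorescein reading, a few minutes at a visit that already includes slit-lamp work.

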##### Ocular Surface Disease Index (OSDI)

The OSDI is the primary outcome measure of subjective symptoms in this trial. It is the most commonly used questionnaire for patients with DED in clinical trials. The OSDI has been validated to measure the severity of DED, and it comprises psychometric symptoms related to DED [40]. Owing to its strong establishment in DED, a consensus to use the OSDI was reached by a related committee [15].

The OSDI measures the frequency of symptoms, environmental triggers, and vision-related quality of life within 1 week. It comprises 12 questions, each of which is graded on a scale of 0–4, where 0 indicates none of the time, 1 as some of the time, 2 as half of the time, 3 as most of the time, and 4 as all of the time [40]. The total OSDI score is calculated as follows: OSDI = [(sum of scores for all questions answered) × 100]/[(total number of questions answered) × 4]

Thus, the OSDI score ranges from 0 to 100; the higher the score, the worse the quality of life. According to OSDI scores, patients can be categorized as having normal (0 to 12 points), mild (13 to 22 points), moderate (23 to 32 points), or severe (33 to 100 points) ocular surface disease. In our trial, patients with OSDI scores ≥ 23 points will be included, meaning that those who have moderate-to-severe symptoms will all be included. The OSDI score will be measured at screening, week 6, week 12, and week 14, and the changes in OSDI from screening to week 12 will be the primary outcome of this trial.

#### 2.6.2. Secondary Efficacy Outcome

##### Fluorescein Corneal Staining Score (FSC)

Ocular staining is used to diagnose DED, assess its severity, and measure its clinical response to therapy. It is one of the most frequently used outcome measures in clinical trials. In our study, fluorescein staining will be evaluated to measure the severity of ocular surface disease using standardized methods and the Oxford grading system [41]. After fluorescein instillation, both eyes will be examined under a slit-lamp microscope (BQ-900; Haag-Streit, Bern, Switzerland) using standard settings. The same investigator will evaluate the corneal staining score throughout the trial period. The grades will range from 0 to 5: 0, absent (dot count 0); 1, minimal (dot count 10); 2, mild (dot count 32); 3, moderate (dot count 100); 4, marked (dot count > 316); and 5, severe (dot count > 316). The fluorescein corneal staining score is an inclusion criterion in our study, and patients with an Oxford grading ≥ 2 will be included. Fluorescein corneal staining will be conducted at screening, week 6, week 12, and week 14 to observe changes after the administration of trial medications.

##### Schirmer’s Test

Schirmer’s test (without anesthesia) will be performed to measure tear secretion in patients with DED. It will be conducted using a standardized process that involves bending the Schirmer strip at the notch and asking the participant to look up and pull down their lower eyelid. Next, we will hook the bent end of the strip over the center of the lower eyelid, with the eye gently closed for 5 min. The length of wetting from the notch will be measured in millimeters [42]. The Schirmer test without anesthesia is a well-standardized measurement of evaluating stimulated reflex of tear flow and the cut-off values of ≤10 mm/5 min for diagnosing dry eye, as reported in a previous study [39].

